**Communication partners**		
*Primary outcomes*		
Coping with hearing loss (HHDI ‘reactions of others’ scale) [80]	X	X
Change from hearing aid use (IOI-HA-SO) [67]		X
Change from communication strategies (IOI-AI-SO) [67]		X_i_
Quality of life (CarerQoL) [81]	X	X
Evaluation of intervention		X_i_
*Secondary outcomes*		
Chronic fatigue (FAS) [74]	X	X
Depression (CES-D) [79]	X	X
Health (subjective health, EQ-5D) [69]	X	X
*Covariates*		
Demographic characteristics (e.g. age, gender)	X	
Relationship with patient (sort and quality of relation)	X	X
Self-efficacy (G-SES) [82]	X	X
**Costs**		
Healthcare use (iMCQ) [83]	X	X
Intervention costs (occupational therapists, travel costs, time communication partner)		X_i_
Costs informal care (SF-HLQ, time spent on care for communication partner)	X	X
Proxy: Travel time and expenses	X	
Proxy: Time spent on care giving for communication partner	X	X

X_i_ Assessed in intervention group only.

#### Primary outcome measures

*Difficulties with hearing aid use and maintenance* will be measured with questions on problems with hearing aid use and maintenance, e.g. “How difficult is it for you to insert your hearing aid?” or “How difficult is it for you to change your hearing aid batteries?”. Questions on *hearing aid fitting, hearing aid use and satisfaction* will be based on the Questionnaire for evaluation of hearing aid fitting, e.g. hours of hearing aid use, use of hearing aids in different situations, and appreciation of hearing aids [84]. *Self-reported change from hearing aids* is measured with the Dutch version of the widely used International Outcome Inventory for hearing aids (IOI-HA) [65,66,85]. The Communication Profile for the Hearing Impaired (CPHI) is an instrument to measure coping behavior related to hearing impairment and is divided into two domains: ‘Communication Strategies’ and ‘Personal Adjustment’ [68]. The ‘Communication Strategies’ domain of the Dutch 35-item version of CPHI will be used to measure *Communication* (coping behavior in communicative situations) and consists of three subscales: ‘Maladaptive Behavior’; ‘Verbal Strategies’ and ‘Non-verbal Strategies’ [68]. *Self-reported change from communication strategies* reported by the participant is measured with the Dutch version of the International Outcome Inventory for alternative strategies (IOI-AI) [67]. Both measures have been used for evaluation of communication programs by, e.g. Kramer et al. (2005) and Hickson et al. (2005) [41,48]).

#### Secondary outcome measures

Secondary outcomes will be coping, quality of life, health, fatigue, loneliness, participation and autonomy. First, the domain ‘Personal Adjustment’ of the CPHI will be used to assess change in *adjustment to hearing loss* and consists of three subscales: ‘Self-Acceptance’, ‘Acceptance of Loss’ and ‘Stress & Withdrawal’ [68]. Second, the Low Vision Quality Of Life (LVQOL) questionnaire is used to assess *vision-related quality of life outcomes* of participants [70,71]. The LVQOL consists of four scales: Basic aspects of vision, vision-related Mobility, Adjustment to vision loss, Reading and fine work. *Health* was measured with an item on subjective health and with the Euroqol 5 Dimensions (EQ-5D) questionnaire to measure health status [69]. *Fatigue* is assessed with the Fatigue Assessment Scale [74]. To measure *participation*, a number of items of the Dutch ICF Activity Inventory will be selected from the participation domain ‘Interpersonal interactions and relationships’, e.g. with regard to communication and understanding of DSL [75]. Furthermore, an item on withdrawal from social activities was included: “Are there any activities you withdraw from because of your dual sensory impairment?”. *Autonomy problems* will be assessed with the 9-item version of the Patient Autonomy Questionnaire (PAQ) [76]. Feelings of *emotional and social loneliness* will be measured with the 11-item Loneliness Scale [72]. Examples of the 11 items of this scale will be “I miss heaving a really close friend” (emotional loneliness) and “I can call on my friends whenever I need them” (social loneliness). The DSL protocol was evaluated with the questions: “Are you satisfied with the advice of the OT?”, “Would you recommend the DSL protocol to other DSL patients?”, “Are you satisfied with the treatment?” and “Are you satisfied with the results?”.

#### Independent variables

In addition, *patient* and *disease characteristics* will be assessed. Information on age, gender, education level, living arrangement (living alone or with a partner), comorbidity, eye condition (e.g. macular degeneration, diabetic retinopathy, glaucoma), ear condition (e.g. presbycusis, tinnitus) and hearing acuity (speech-reception-threshold in noise, defined as the signal-to-noise ratio corresponding to 50% intelligibility) will be collected by research assistants. Visual acuity and other relevant data, such as the eye condition, will be obtained from the patient’s files at the low vision rehabilitation centers with the patient’s consent. *Cognitive impairment* is assessed with the six-item screener derived from and comparable to the full Mini-Mental State Examination (MMSE) [78]. Finally, the Dutch version of the Center for Epidemiological Studies-Depression scale (CES-D), a general indicator of *depressive mood*, is used to assess the presence of depressive symptoms, which may influence the outcome of the study [79]. Participants will be asked if major life events have occurred between baseline and follow-up.

#### Communication partner

The HHDI ‘reactions of others’ scale assesses attitudes towards the hearing impaired partner and has been used to measure *coping with hearing loss*[80]. *Self-reported change from hearing aids* and *self reported change from communication strategies* reported by the communication partner will be measured with the Dutch versions of the International Outcome Inventory for hearing aids (IOI-HA-SO) and the International Outcome Inventory for alternative strategies (IOI-AI-SO) [67]. *Health* was measured as subjective health and with the EuroQol 5 Dimensions (EQ-5D) [69]. *Evaluation of the DSL protocol* with questions: “Are you satisfied with the advice of the OT?”, “Are you satisfied with the treatment?”, and ”Are you satisfied with the results?”. *Chronic fatigue* was assessed with the Fatigue Assessment Scale (FAS) [74]. *Self-efficacy* is measured with the General Self-Efficacy Scale (GSES) divided in three subscales: Initiative, Effort and Persistence [82]. *Depressive symptoms* will be assessed with the Dutch version of the Center for Epidemiological Studies-Depression scale (CES-D) [79].

#### Costs

In a bottom-up price calculation all costs (intervention, health care costs, costs of formal and informal care) will be calculated for both the intervention and control group. Intervention costs include participation of the OT (time, travel time and expenses), participation of the communication partner (time, travel time and expenses). Healthcare costs include costs of medication and consultations of health care providers. The volume of will be measured with the iMTA Medical Consumption Questionnaire (iMCQ) [83] and costs will be evaluated according to the prices suggested in the guidelines for economic evaluation in The Netherlands [86]. If guidelines are not available, costs will be estimated.

#### Statistical analysis

Data will be analyzed according to the intention-to-treat principle. Linear mixed models for continuous outcomes and generalized linear mixed models for counts and categorical outcomes will be used to assess treatment effects with respect to primary and secondary outcome measures. Treatment effects will be assessed according to the analysis strategy as described by Winkens et al. [87-89] and is defined as the treatment allocation*time interaction. To account for correlatedness of outcomes within the same therapist, a random intercept for therapist is included in the model.

For participants who are not treated according to the protocol, intention-to-treat analyses will be compared to per-protocol analyses. Data will be analyzed using the software package SPSS 20 for Windows.

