#### Randomization

After baseline measurements, participants will be randomly allocated (stratified by therapist) to either the intervention or control group, by means of computer-generated tables. Trained OTs employed by the participating low vision multidisciplinary rehabilitation institutions in the Netherlands and in Belgium will provide therapy for older adults with DSL and their communication partner (i.e. the intervention group) according to the newly developed DSL protocol. To prevent unequal distributions of participants in the control and intervention groups among OTs, participants will be stratified within working areas of OTs before randomization resulting in eight strata, one for each of the eight participating OTs (four OTs from Bartiméus, two OTs from Visio and two OTs from Blindenzorg Licht en Liefde). Block randomization will be performed in blocks of two to ensure equal group sizes in each stratum. Randomization will be performed by an independent researcher using a computer-generated allocation scheme so that the researcher who will analyze the data is blinded (trained research assistants will enter all data into a laptop computer using codes). All participants will be informed about the allocation. In case a participant is allocated to the treatment group, an email will be sent to inform the designated OT. Treatment will take place in the participant’s home in 3–5 appointments, depending on the individual needs of the participant and/or proxy. All participants have received low vision rehabilitation and hearing aid fitting before entering the study. Using a waiting list procedure, participants in the control group will be offered treatment after 3-month follow-up measurements.

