#### Data collection

Measurements will include face-to-face structured interviews and will be performed by trained research assistants in a quiet room in the home of the participant at baseline and at 3-months follow-up. Data collection will take about two hours per measurement. The software program Blaise Enterprise 4.7 (Heerlen, the Netherlands) will be used to directly enter data into laptop computers. Communication partners will be asked to fill in a written questionnaire at baseline and at 3-months follow-up. To measure the ability of understanding speech in noise (speech-reception-threshold in noise), a speech-in-noise test developed by Smits et al. (2013) will be included in the baseline measurements [64]. In the present study, the test will be programmed on laptop computers and performed with headphones (Speedlink Medusa). Digit triplets, uttered in Dutch, will be presented in noise. The participant will repeat the triplet he/she has heard out loud, after which the research assistant will type the digits into the laptop computer and the next digit triplet will be presented to the participant.

Three months after data collection, all participants (including non-compliant participants) will be approached for follow-up measurements.

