**DSL patients**		
*Primary outcome measures*		
Hearing aid fitting, hearing aid use and satisfaction	X	X
Difficulties with hearing aid use and maintenance	X	X
Change in hearing aid use (IOI-HA) [65,66]		X
Change from communication strategies (IOI-AI) [67]		X_i_
Communication (CPHI-communication strategies) [68]	X	X
*Secondary outcomes*		
Health (subjective health)	X	X
Health related quality of life (EuroQol-5 Dimensions (EQ-5D)) [69]	X	X
Coping with hearing impairment (CPHI-personal adjustment) [68]	X	X
Vision-related quality of life (LVQOL) [70,71]	X	X
Loneliness (Loneliness scale) [72,73]	X	X
Fatigue (FAS) [74]	X	X
Participation (parts of D-AI-interpersonal interactions and relationships) [75]	X	X
Autonomy (PAQ) [76]	X	X
Evaluation of intervention		X_i_
*Covariates*		
Patient characteristics (e.g. age, gender, education, living arrangement)	X	
Disability characteristics (eye condition, VA, self-perceived vision (VFQ25-general vision subscale [77]), hearing condition, hearing loss (speech-reception-threshold in noise))	X	
Cognition (6-item screener MMSE) [78]	X	
Depressive symptoms (CES-D) [79]	X	X
Major life events between baseline and follow-up		X

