#### Sample size

Power calculations are based on expected progress in use of communication strategies (the Communication Strategies Scale of the Hearing Handicap and Disability Inventory), which has been the primary outcome of previous studies in persons with hearing loss [41]. In a previous RCT by Kramer et al. (2005) on the effectiveness of a home education program for older adults with hearing impairment only, the mean difference in communication skills between the intervention and control group was about 0.5 (SD = 0.8) [41]. Sample size calculations of this RCT are based on a linear mixed models and confirmed by some simulations (data not shown). Sixty-two participants per arm, with adjustment for clustering by 8 therapists in the intervention condition, provide a power of 0.80 (1-β) with alpha 0.05 (two-sided significance level), to detect a 0.5 difference between trial arms after 3 months (corrected for the differences at baseline), after taking into account a 20% dropout rate.

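### The allocation-by-time effect, as ordinarily read, is a difference in mean change; adjusting continuous outcomes for the baseline already collected would be more precise at no cost

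*Protocol article*

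**What the plan says.** The Statistical analysis section plans "Linear mixed models for continuous outcomes and generalized linear mixed models for counts and categorical outcomes". For primary and secondary outcomes alike the treatment effect "is defined as the treatment allocation*time interaction". The strategy is taken from cited methodological papers ("Treatment effects will be assessed according to the analysis strategy as described by" precedes the citations), which the article does not reproduce. The only random effect named is for the therapist: "a random intercept for therapist is included in the model". No baseline covariate, constraint on baseline means or within-patient covariance is stated.

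Three other places bear on this:

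- **Data collection:** participants are measured "at baseline and at 3-months follow-up", so there are two time points. In Table 2 the CPHI communication strategies domain is marked at both ("Communication (CPHI-communication strategies) [68] X X"). The IOI-HA and IOI-AI are marked at follow-up only.
- **Randomization:** "After baseline measurements, participants will be randomly allocated". Baseline scores therefore precede allocation.
- **Sample size:** the detectable 3-month difference is described as "corrected for the differences at baseline", without saying whether by subtraction or by regression.

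**The concern.** Because allocation comes after baseline, the two arms have the same expected baseline mean, and any observed difference is chance. A model with allocation, time and their interaction ignores this and gives each arm its own baseline mean. With two time points its interaction term is follow-up minus baseline in one arm, less the same in the other. Baseline is thus subtracted with a coefficient of 1. The efficient coefficient is the regression slope, which equals rho when the two variances are equal and so lies below 1. A chance baseline difference is then over-corrected in the individual trial. Over repeated trials the estimate stays unbiased but varies more than it needs to.

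What is at stake is precision: wider confidence intervals and lower power for continuous outcomes with a baseline, including the CPHI communication strategies domain among the primary outcomes. The data that would recover the precision are already being collected.

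**Working it through.** **Inputs from the article.** Difference 0.5, SD 0.8, 62 per arm, 20% dropout (62 × 0.8 = 49.6 evaluable per arm), two-sided alpha 0.05, power 0.80, 8 therapists with clustering in the intervention arm (all from Sample size).

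**Assumed, because not given.** rho, shown from 0.3 to 0.9; equal SD at both times; where an SE is computed, 0.8 is taken as the SD of raw scores. The article does not say whether 0.8 is a raw-score or a change SD.

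**Step 1: does the stated sample size reveal the estimator?**

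- Plain comparison of means: n = 2 × 7.849 × 0.8² / 0.5² = 40.2, so 41 per arm; 41 / 0.8 = 51.25, so 52. The stated figure is 62.
- Allowing for therapist clustering in the intervention arm only, with cluster size 49.6 / 8 = 6.2 and SD 0.8 for the analysed quantity, an ICC of about 0.09 gives 80% power: variance = 0.64 × (1 + 5.2 × 0.09) / 49.6 + 0.64 / 49.6 = 0.0318.
- A change score with raw SD 0.8, rho 0.4 and no clustering also gives 62: n = 2 × 7.849 × 0.64 × 1.2 / 0.25 = 48.2, so 49; 49 / 0.8 = 61.25, so 62.

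So 62 is attainable in more than one way. It does not show which estimator was powered.

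**Step 2: variances with complete data, n per arm.**

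- Difference in mean change: (2/n) × SD² × 2(1 − rho)
- Adjusted for baseline: (2/n) × SD² × (1 − rho²)
- Ratio, adjusted to change: (1 − rho²) / [2(1 − rho)] = (1 + rho)/2. The SD cancels.

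**Step 3: with dropout.** If a fraction f is followed up at random and the mixed model keeps everyone's baseline, the per-arm variances are:

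- free baseline means: SD² × [(1 − rho²)/(fn) + (1 − rho)²/n]
- common baseline mean: SD² × (1 − rho²)/(fn)

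The ratio is (1 + rho) / [1 + rho + f(1 − rho)], which returns (1 + rho)/2 at f = 1. At f = 0.8 and rho 0.5: 1.5 / (1.5 + 0.4) = 0.79.

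**Step 4: simulation.** 62 per arm, 6,000 runs per setting, difference 0.5, SD 0.8, known covariance, no therapist clustering. The ratio is common baseline mean to free baseline means.

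| rho | Complete data, formula | Complete data, simulated | 20% dropout, formula | 20% dropout, simulated |
|---|---|---|---|---|
| 0.3 | 0.65 | 0.64 | 0.70 | 0.70 |
| 0.5 | 0.75 | 0.74 | 0.79 | 0.78 |
| 0.7 | 0.85 | 0.84 | 0.88 | 0.88 |
| 0.9 | 0.95 | not run | 0.96 | not run |

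With complete data the free-baseline interaction and the difference in mean change were identical in every run. At rho 0.5 the SE was 0.144 for both, against 0.124 for both ANCOVA and the common-baseline model. With 20% dropout at rho 0.5 it was 0.155 for the free-baseline model (0.159 for a change score in completers only) and 0.137 for the common-baseline model. All estimators averaged about 0.5, so none was biased.

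**The case against.** The strongest reply is that the article does not say that the baseline means are free. A model with time and allocation-by-time but no allocation main effect also expresses its treatment effect as that interaction, and it is one of the two remedies proposed here. The choice is left to a cited strategy that is not shown, and a journal article may leave such detail to a fuller document. The baseline correction mentioned under Sample size fits covariate adjustment as well as subtraction. All of this stands, and it limits certainty about what will be run. It does not remove the point. An interaction is ordinarily fitted with both main effects, and dropping one is a deliberate step that authors usually state. One sentence settles the matter under either reading.

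It is also fair to say that the change-score analysis is valid, and that the gain is small when rho is high: 5% of the variance at rho 0.9.

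A reader might go further and infer that adjustment restores the stated 80% power. With rho 0.5, therapist ICC 0.05 and a test on 7 degrees of freedom, power does rise from 0.70 to 0.80. The same inputs on about 21 degrees of freedom, an approximation that treats clustering as confined to the intervention arm as Sample size describes it, give 0.79 and 0.88. The result therefore depends on the chosen degrees of freedom. Neither these nor rho nor the ICC are in the article, which does not support a claim of lost or restored power.

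**Conclusion.** The point holds as a recommendation on efficiency and clarity. For continuous outcomes measured at both times, and on the ordinary reading of the model, the complete-data variance is 2/(1 + rho) times what baseline adjustment would give. That is 1/0.75 = 1.33 times at rho 0.5 and 1/0.95 = 1.05 times at rho 0.9. With 20% dropout the penalty is somewhat smaller. The result rests on an assumed rho, equal variances at the two times, random dropout and an allocation main effect in the model. If the cited strategy already uses a common baseline mean, or baseline is already a covariate, nothing is lost.

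Two wider readings should be resisted. The plan is not biased or invalid, since randomisation protects the interaction estimate. Nor does the variance ratio cover all outcomes: it is derived for continuous scores, does not carry over to the generalized linear mixed models, and has no meaning for the IOI-HA and IOI-AI, which have no baseline.

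**What to change.** In the Statistical analysis section, for continuous outcomes measured at baseline and 3 months (for example CPHI communication strategies), define the treatment effect as the arm difference at 3 months adjusted for the baseline score. Name one of two equivalent routes:

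- **ANCOVA:** 3-month score on allocation and baseline score, with therapist in the model.
- **Longitudinal model with a common baseline mean:** time and allocation-by-time, no allocation main effect, the therapist term as planned, and a stated within-patient covariance between the two measurements. Without that covariance the model does not use a patient's own baseline, and the gain is lost.

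State also which form of baseline correction the sample size calculation used, so that the powered and planned analyses can be seen to match. If the cited strategy already contains the adjustment, saying so is enough.

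The cost is one or two sentences. No new data, visits or participants are needed, and the sample size need not change.

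### The therapist random intercept cancels from the allocation-by-time effect, so the stated model does not carry the intervention-arm therapist clustering that the sample size allows for

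*Protocol article*

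**What the plan says.** All places are in the protocol article.

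- **Statistical analysis.** The treatment effect "is defined as the treatment allocation*time interaction". One term is named for therapists: "To account for correlatedness of outcomes within the same therapist, a random intercept for therapist is included in the model". The wider strategy is left to cited references. No patient random effect, and no therapist effect on treatment or on time, is named.
- **Randomization.** Patients are "stratified within working areas of OTs before randomization resulting in eight strata, one for each of the eight participating OTs". Within strata, "Block randomization will be performed in blocks of two to ensure equal group sizes in each stratum". Baseline is measured before allocation. Under the waiting-list arrangement, "participants in the control group will be offered treatment after 3-month follow-up measurements".
- **Sample size.** The target is "Sixty-two participants per arm, with adjustment for clustering by 8 therapists in the intervention condition", for 80% power at two-sided 0.05, a difference of 0.5 (SD 0.8) and 20% dropout. No ICC and no within-patient correlation are given.

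**The concern.** Through the intervention, a therapist can influence outcomes only in treated patients and only after baseline. Controls are not offered treatment until their 3-month measurement is done. The clustering that matters is therefore between-therapist variation in the treated arm at follow-up, and this is the clustering that the Sample size section describes.

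A random intercept for therapist represents something else: a level common to all patients in a therapist's area, treated or not, before and after. It is added for the purpose of handling therapist correlation, but it cannot do so for the effect being tested. At stake is whether the stated 5% error rate holds for the continuous outcomes measured at both visits.

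**Working it through.** **1. The plan's own figure.** Inputs from Sample size: difference 0.5, SD 0.8 (variance 0.64), power 0.80, two-sided 0.05, dropout 20%.

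- No clustering: n = 2 × (1.960 + 0.842)² × 0.64 / 0.25 = 40.2, so 41 per arm. With dropout: 41 / 0.8 = 51.25, so 52 per arm.
- The plan asks for 62. Without clustering, 62 × 0.8 = 49.6 evaluable per arm would give power 0.875. The extra ten per arm are therefore taken as the clustering allowance.
- The figure of 62 cannot be reproduced from stated inputs, because no ICC is given. Back-solving with a design effect DE in the treated arm only: 40.2 × (1 + DE) / 2 = 49.6 gives DE = 1.47. With m = 49.6 / 8 = 6.2 treated patients per therapist, DE = 1 + (m − 1) × ICC gives ICC = 0.47 / 5.2 = 0.09. This is an assumption, not a figure from the plan.

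**2. Cancellation.** Write an outcome as fixed effects + therapist intercept + patient effect + residual. The allocation-by-time effect is the mean change in the treated arm minus the mean change in controls. Each patient's change subtracts two values with the same therapist intercept, so the intercept disappears.

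A generalized least-squares check used 8 therapists, 50 evaluable per arm (six therapists with 6 and two with 7 per arm), and patient and residual variances of 0.32 each, so a within-patient correlation of 0.5.

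| Therapist variance | SE, shared intercept | SE, effect on treated patients at follow-up |
|---|---|---|
| 0 | 0.1600 | 0.1600 |
| 0.0576 (= 0.09 × 0.64) | 0.1600 | 0.1812 |
| 0.3 | 0.1600 | 0.2513 |
| 1.0 | 0.1600 | 0.3881 |

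Coding the intercept for the intervention arm only also leaves 0.1600 throughout. If the two arms are given a common baseline mean, the shared intercept still cancels (0.1386 throughout). An intervention-only intercept is then partly carried (0.1436 against 0.1386 at variance 0.0576).

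**3. Size when a patient effect is modelled.** Let ρ be the within-patient correlation, v = 2 × 0.64 × (1 − ρ) the variance of a change, τ² = ICC × 0.64, n = 50 per arm and n_k the treated patients of therapist k. Total variance is held at 0.64, which is why the SE at ρ = 0.5 is 0.178 here and 0.1812 above, where τ² was added on top.

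- Model SE = √(2v / n)
- True SE = √(2v / n + τ² × (Σn_k² / n² − 1 / n))
- Σn_k² / n² = (6 × 36 + 2 × 49) / 2500 = 0.1256, so the bracket is 0.1256 − 0.02 = 0.1056. At ICC 0.09 the added variance is 0.0576 × 0.1056 = 0.00608.

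| ρ (assumed) | Model SE | True SE | Ratio | Type I error, 40,000 simulated trials |
|---|---|---|---|---|
| 0.3 | 0.189 | 0.205 | 1.08 | 7.0% |
| 0.5 | 0.160 | 0.178 | 1.11 | 7.8% |
| 0.7 | 0.124 | 0.146 | 1.18 | 9.7% |

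Over ICC 0.03 to 0.15 and ρ 0.3 to 0.7, simulated type I error runs from 5.6% to 13.0%. With no therapist effect it is about 5%.

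**4. Size when therapist is the only random effect.** The model SE is √(4 × 0.64 / 50) = 0.226, above every true SE in the range. Simulated type I error is 3.8% or less in every scenario.

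**The case against.** The strongest reply is that the direction of the error depends on a term the article does not mention. Read literally, the Statistical analysis section has one random effect, therapist, and step 4 shows that such a model is conservative. Reading the text as implying a patient effect, but not a therapist-by-treatment effect, treats two silences differently. This stands as a condition. A reader might infer that the standard errors are too small whatever the model; the document does not support that. Under either reading, however, the therapist intercept contributes nothing to the tested contrast.

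A second reply is that the full model sits in cited references that are not available here, and that the sample-size simulations are not shown. A further random effect may exist there. That limits certainty, but the article does not leave the therapist structure open: it names a term and its purpose, and that term cannot serve the purpose.

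A reader might also infer that true power is well below 80%. At ICC 0.09, dividing 0.5 by the true SE gives 2.81 at ρ = 0.5 and 3.42 at ρ = 0.7. Referred to non-central t distributions with 7 to 18 degrees of freedom, these give power of roughly 67% to 76% and 83% to 90%. The answer turns on a correlation that the plan does not state, so no power shortfall can be claimed.

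Nor should the result be stretched to every outcome. Exact cancellation was shown for the linear model with complete data. It was not shown for the generalized linear mixed models or for outcomes measured only at follow-up. Finally, calling the two sections contradictory goes too far. Both recognise therapist clustering; the analysis term does not match the design allowance.

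**Conclusion.** The point holds as a mismatch between the analysis and the design. For continuous outcomes measured at both visits, the therapist intercept drops out of the treatment effect (approximately so under the expected dropout), and the intervention-arm clustering built into 62 per arm is not carried by the stated term.

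The test is anti-conservative on two conditions: within-patient correlation is modelled, and therapists differ in effect, as the Sample size section itself assumes. The understatement is then moderate: a true SE about 8% to 18% above the model SE and type I error of about 7% to 10%, at the back-solved ICC of 0.09. The ICC, the correlations and the rounding to 50 evaluable per arm are assumptions made here.

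**What to change.** Replace the therapist sentence in Statistical analysis with a specification that names:

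- a patient random effect, or correlated residuals within patient;
- an intercept for the therapist stratum;
- a therapist random effect on the intervention-by-follow-up term, acting only in treated patients after baseline (a partially nested structure);
- Satterthwaite degrees of freedom, because there are only eight therapists.

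In Sample size, state the ICC and within-patient correlation behind 62 per arm, and recheck the stated 80% power under this model.

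The change needs no new data. It costs somewhat wider confidence intervals, and the added variance component will be imprecisely estimated from eight therapists with about six treated completers each.
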